## Abstract

Background: Aging is a natural process associated with many functional and structural changes. These changes may include impaired self-regulation, changes in tissues and organs. Aging also affects mood, physical status and social activity. There are adverse changes in cognitive behavior, perceived sensation and thinking processes. Regular physical activity can alleviate many health problems; yet, many older adults are inactive. Yoga is one of the scientific and popular lifestyle practice considered as the integration of mind, body and soul. Results of previous studies reported positive effects of yoga on multiple health outcomes in elderly. However, there is scarcity of scientific information where yoga’s effect is examined on over well-being and on multiple health outcomes simultaneously in elderly. This protocol describes methods for a 12-week yoga-based intervention exploring the effects of yoga on well-being in physically inactive elderly living in community. Methods and analysis: This two group parallel single blind randomized controlled trial that will be conducted at a designated facility of R.D. Gardi Medical College, Ujjain, Madhya Pradesh, Central India. A 12-week 60-min yoga intervention three times weekly is designed. Comparison group participants will undergo a 60-min program comprising light exercise focusing on conventional stretching to improve mobility. After screening, 144 participants aged 60–80 years will be recruited. The primary outcome is subjective well-being. Secondary outcomes include mobility, fall risk, cognition, anxiety and depression, mood and stress, sleep quality, pain, physical activity/sedentary behavior and cardio-metabolic risk factors. Assessments will be conducted at baseline (0 week), after the intervention (12+1 week) and at follow-up (36+1 week). Intention-to-treat analyses with mixed linear modeling will be applied. Discussion: Through this trial, we aim to determine whether elderly people in the intervention group practicing yoga show more favorable primary (well-being) and secondary outcomes than those in the light exercise focusing on conventional stretching group. We assume that yoga may be practiced to maintain health, reduce particular symptoms commonly associated with skeletal pain, assist in pain relief and enhance well-being. We anticipate that practicing yoga will improve well-being and mental health and may lead to significant improvement in depression, pain and sleep quality.Ethics and dissemination: This study is approved by the Institutional Ethics Committee of R.D. Gardi Medical College, Ujjain, IEC Ref No. 09/2018. All participants would be provided with written and verbal information about the purpose of the project and would be free to withdraw from the study at any time. Refusal to participate in the study would not have any negative consequences. Confidentiality of the information of each participant would be ensured. Knowledge obtained would be disseminated to stakeholders through workshops, meetings and relevant scientific conferences.Trial Registration: The trial is prospectively registered with the Indian Council of Medical Research Trial Registry CTRI/2018/07/015051.

## 1. Introduction

Aging is a natural process associated with many functional and structural changes [1,2]. These changes may include impaired self-regulation, changes in tissues and organs. Aging also effects mood, physical status and social activity, adverse changes in cognitive behavior, changes in perceived sensation and thinking processes [3]. The world’s population is aging, and more people are living longer. It is estimated that the proportion of the individual over 60 years will almost double from 12% to 22% between 2015 and 2050 [4] thus also increasing in prevalence of non communicable disease and non-fatal disabilities and in ultimately increases the dependency.

Physical activity (PA) is a protective factor for non communicable diseases such as cardiovascular disease, stroke, diabetes and some types of cancer [2]. PA is also associated with improved mental health [3], delay in the onset of dementia [5] and improved quality of life and wellbeing [5,6]. The health benefits of PA are well documented with higher levels and greater frequency of PA being associated with reduced risk and improved health in a number of key areas [7].

It is widely documented that regular physical activity in elderly can help in delaying and preventing a wide range of health problems including cardiovascular disease, stroke, diabetes and some types of cancer [6,7,8]. Regular physical activity can further show improvements in conditions such as pain, mobility, mood disorders, mental health, sleep quality, depression and anxiety [9,10]. Inspite of these known benefits, studies have documented that with the increase in age, the level of physical activity is decreasing [11]. The decrease in physical activity can have major negative consequences on the non- communicable diseases [7], which is to continue to be the one of the leading risk factor for mortality [12]. It is important to focus on interventions that improve healthy aging, reduces disability onset outcomes and enhances life quality.

The evidence from recent studies has identified the elderly’s interest in different type of physical activity that are simple, easy and help them in developing well-being and internal satisfaction than focused on fitness and appearances [13,14,15,16,17]. Well-being, which is consisted of physical, psychological and social components [18], and high well-being are associated with low prevalence of non communicable diseases, healthy aging and longevity [19,20]. 

Yoga, is one of the scientific and popular lifestyle practices considered as the integration of mind, body and soul [21]. Yoga has been proven to be extremely beneficial for physical, mental and social health since ancient times, and it is gaining popularity worldwide very rapidly [21,22].

Several studies conducted across the globe have demonstrated the positive effects of yoga on the number of health outcomes that concerns elderly such as improvements in depression and anxiety [13,23,24,25,26,27], mood and stress [25,28], pain reduction [29,30], enhanced sleep quality [13,25,26,30,31], balance resulting in fall prevention [23,27,32,33] cognition [31,34] and cardio metabolic health [17,28,30,35]. Studies have also reported improvement in the subjective well-being [36,37]. In elderly, yoga based intervention helps in maintaining breathing and heart rate, decreasing blood pressure, lowering cortisol levels and helps in increasing blood flow, which further helps in restoring autonomic regulatory reflex mechanisms associated with stress [30].Yoga appears to be one of the viable interventions to reduce inflammation in different chromic conditions [38]. Studies also reported the positive effect of yoga on inflammatory markers such as cytokines interleukin-6 (IL-6) and tumor necrosis factor (TNF) and the acute-phase protein C-reactive protein (CRP) [38,39].With few exceptions [31,40,41,42], the current evidence is limited primarily to ‘feasibility’, ‘exploratory’ and ‘pilot’ studies; many of which have been conducted in residential care homes. Moreover, most studies of yoga and cognition/mood have not included older adults. What is now required are rigorously designed and adequately powered community-based trials that include long-term assessments of multiple and diverse health outcomes.

### 1.1. Rationale

Injury related hospitalizations are on the increase in the elderly population. Fall injuries are more prevalent in elderly, which accounts for 10–15% of all emergencies. Falls are also the leading cause of injury-related death in the elderly as well. Healthy is considered as the process of developing and maintaining the functional ability that enables wellbeing. Though normal exercise is recommended to prevent several non communicable diseases [43], however due to its focus on flexibility and balance yoga can help more in reducing the risk of fall-related injuries [16,42]. Further with its multidimensional and holistic focus on the physical, mental and spiritual approach, yoga may be more suitable and manageable than normal exercise for elderly [44]. Further yoga emphasized on breath regulation, mindfulness and maintenance of postures, which is not a part of normal exercises [45]. Studies previously conducted, compared the effect of yoga on non-active controls [46]. No studies have been reported where effects of yoga on subjective well-being is compared to light exercise designed to improved mobility among elderly in a community setting in developing countries.

The present study protocol proposes the methodology of an RCT that aims to improve the health and well-being of elderly between 60–80 years through yoga-based interventions. We will explore the effects of participation in a yoga-based program on subjective well-being (primary study outcome) and healthy aging in older adults; the primary outcome will be measured using the life satisfaction index, version Z (LSI-Z) and satisfaction with life scale (SWLS). We will assess whether the practice of yoga results more favorable health outcomes than the practice of light mobility exercises. The potential public health implication of this study will be immense if the study results able to demonstrate that yoga has a positive effect on elderly’s well-being, mobility and cognition. This may further help in the prevention and treatment of age related diseases and conditions and development of future preventive interventions for the elderly in community setup. We are also anticipating that the project will also empower participants to initiate and continue yoga-based activities beyond the intervention. We are anticipating that the benefits of the intervention will be felt by the participants, their families and society in the form of (anticipated) lower health costs.

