### 2.7. Outcomes Variables

#### 2.7.1. Primary

Well-being will be measured subjectively using the 13 items life satisfaction index, version Z (LSI-Z) [50,51]. Five core components of life satisfaction are measured in the life satisfaction index, namely zest, resolution and fortitude, congruence between desired and achieved goals, positive self-concept and mood tone [52]. Subjective well-being will also be assessed by using a five-item satisfaction with life scale (SWLS) that measures global judgments of one’s life satisfaction [53]. On this scale, the participants show how much they agreed with or disagreed with each item on a scale of 7.

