#### 2.7.3. Sample Size

The calculation of sample size for this study is based on the effect size reported in a six month long RCT where results of Iyenger yoga on elderly was compared with walking [42]. Based on this study we anticipate that the mean difference (effect size) of around 0.2 on our primary outcome that is well-being in yoga intervention group compared to exercise group. With 80% power, two-tailed significance for the primary between-group comparisons and 1:1 allocation, a total sample of 120 participants is estimated. Assuming a 6-month dropout rate of 20% [72], the total number of participants required at baseline will be 144.

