### 2.8. Data Collection

#### 2.8.1. Time Points

Primary and secondary outcomes will be measured at baseline (0 week), post-intervention (12+1 week) and at end point (36+1 week). The assessments will include basic demographic-socio-economic information, anthropometrics measurements, primary and secondary outcome measurements and biological sampling (see Figure 1 and Table 1).

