## 3. Statistical Analyses

We will use appropriate parametric (*t*-test and Analysis of variance (ANOVA) and non-parametric (Mann–Whitney U and Kreskas Wallis test) tests to compare the socio-demographic-economic and other base-line characteristics of the two groups. Intention-to-treat (ITT) analyses to examine the effects of the intervention that will be explored using mixed linear modeling, in which group × time interactions will be reported with regression estimates, confidence intervals and effect sizes. Sensitivity analyses will also be performed. The moderating effects of gender and age and the interaction effects of education on cognitive outcomes will be also be examined. A similar plan will be followed for the analysis of secondary outcomes.

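### The primary outcome is two unranked scales at two follow-up visits, and the protocol does not say which scale or visit decides the primary claim

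*Protocol article*

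**What the plan says.** **Scales.** Section 1.1 says that "the primary outcome will be measured using the life satisfaction index, version Z (LSI-Z) and satisfaction with life scale (SWLS"). Section 2.7.1, headed Primary, begins "Well-being will be measured subjectively using the 13 items life satisfaction index, version Z (LSI-Z") and continues "Subjective well-being will also be assessed by using a five-item satisfaction with life scale (SWLS"). Table 1 puts both scales in its single well-being row. None of these places gives a ranking, a composite score or a rule that both scales must succeed.

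**Times.** Section 2.8.1: "Primary and secondary outcomes will be measured at baseline (0 week), post-intervention (12+1 week) and at end point (36+1 week"). Section 1.5 gives the same visits. Neither follow-up is named as primary.

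**Analysis.** Section 3 plans a mixed linear model in which "group × time interactions will be reported with regression estimates, confidence intervals and effect sizes". It names no scale, visit or contrast as decisive, and adds that "A similar plan will be followed for the analysis of secondary outcomes".

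**Sizing.** Section 2.7.3 refers to "two-tailed significance for the primary between-group comparisons" at 80% power, with an effect of about 0.2 on well-being. It attaches this to neither scale nor visit, and prints no numerical alpha.

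**The concern.** A primary outcome is fully defined only when the instrument, the time point and the decision rule are fixed. Here only the construct is fixed.

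The indications of time also pull apart. The objectives (sections 1.2 and 1.3) are framed around a 12-week intervention. Section 2.8.1 calls week 36+1 the end point, and section 2.7.3 uses a 6-month dropout rate.

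Two things are at stake. First, more than one result could support the statement that yoga improves well-being, so the chance of a false primary claim exceeds that of one test, and the choice among results could be made after seeing them. Second, discordant results have no agreed reading. If LSI-Z favoured yoga at week 12+1 and SWLS showed nothing at week 36+1, the protocol would not say whether the trial had succeeded.

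**Working it through.** **Inputs from the article.** Two scales (sections 1.1 and 2.7.1, Table 1); two post-baseline visits (sections 1.5 and 2.8.1); a two-sided test (section 2.7.3); 120 evaluable participants at 1:1, so 60 per arm (section 2.7.3).

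**Assumptions.** A level of 5% per test, because no alpha is printed. Correlation between the scales' test statistics of 0.3 to 0.8, and between the two visits of 0.5 to 0.8, because the article gives none. The article states no error rate, so there is no figure of its own to reproduce.

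**Step 1: how many primary tests?** Section 3 allows two ordinary readings.
- A: one overall group-by-time test per scale, 2 scales × 1 = 2 tests.
- B: the group difference in change read at each follow-up visit, 2 scales × 2 visits = 4 tests.

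**Step 2: independence as the upper reference.** The chance of at least one false positive is 1 − (1 − 0.05)^k.
- k = 2: 1 − 0.95² = 9.75%
- k = 4: 1 − 0.95⁴ = 18.5%

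**Step 3: correlated tests under no effect.** Simulation of correlated normal statistics, at least 1,000,000 draws per setting, counting any |z| > 1.96. For four tests the correlation matrix is the Kronecker product of the scale and visit matrices. In the last column only z > 1.96 in yoga's favour is counted.

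| Reading | Scale r | Visit r | Any false positive | False claim favouring yoga |
|---|---|---|---|---|
| A | 0.5 | – | 9.0% | – |
| A | 0.7 | – | 8.3% | – |
| A | 0.8 | – | 7.8% | – |
| B | 0.3 | 0.5 | 16.9% | 8.5% |
| B | 0.5 | 0.5 | 16.2% | 8.1% |
| B | 0.7 | 0.7 | 13.7% | 6.8% |
| B | 0.8 | 0.8 | 12.0% | 6.0% |

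With two follow-up visits, the overall test in reading A has 2 degrees of freedom. Simulating that form (each chi-square against its 5% point) gives 9.5%, 9.1%, 8.5% and 7.9% at scale correlations 0.3, 0.5, 0.7 and 0.8, so the 8-10% range holds.

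For comparison, one two-sided 5% test has a 5% false-positive rate, of which 2.5% favours yoga. Four independent tests give 9.6% favouring yoga.

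**Step 4: what splitting alpha would cost.** With 60 per arm, the difference detectable at 80% power is (z for 1 − α/2 + 0.842) × √(2/60), and √(2/60) = 0.1826.
- One test, α = 0.05: (1.960 + 0.842) × 0.1826 = 0.51 SD
- Two tests, α = 0.025: (2.241 + 0.842) × 0.1826 = 0.56 SD
- Four tests, α = 0.0125: (2.498 + 0.842) × 0.1826 = 0.61 SD

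At a true difference of 0.51 SD, power is 80%, 71% and 62% respectively. Whether 120 follows from the stated effect of 0.2 is a separate question that this point does not use.

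**The case against.** **The trial is labelled exploratory (section 1.5), and section 3 promises estimates and intervals, not a significance rule.** This softens the point but does not remove it. Section 1.4 states a directional hypothesis of a 20% improvement, and section 2.7.3 sizes a primary comparison at 80% power. A trial with those features needs one defined primary result.

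**A multiplicity procedure can sit in an analysis plan or full protocol that is not shown.** This stands: a reader might infer that the trial has no error control at all, and the article cannot show that. But which scale and visit are primary belongs to the outcome definition. The article does define the outcome, and does so each time with two unranked scales.

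**A reader might infer that the plan prescribes four tests at 5%.** The text does not support that. No alpha is printed, and one overall interaction test per scale is an equally ordinary reading. The four-test figure is therefore one end of the range. It also counts false results favouring the comparison group, so it is about double the risk of a false claim for yoga.

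**A reader might infer that the trial was sized for exactly one comparison.** Section 2.7.3 speaks of comparisons in the plural and names no scale or visit, so it settles neither one nor several.

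**The article could be said to imply a primary already.** LSI-Z comes first and SWLS is introduced with an also, but section 1.1 joins them as equals and both stay under the primary heading. Nor do the objectives settle on week 12: the 12 weeks there is the length of the intervention, and the end-point label and dropout period lean towards the later visit.

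**Conclusion.** The point holds. Subjective well-being is assigned two scales and two follow-up visits, without a deciding pair or a rule for combining the scales, and the indications of which visit matters conflict. This is a badly fixed primary outcome, not a detail left to an analysis plan.

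The inflation is moderate: somewhat under double the nominal error on the two-test reading, and roughly 2.4 to 3.4 times on the four-test reading (12.0/5 to 16.9/5). For a false claim in yoga's favour the four-test ratio is likewise 2.4 to 3.4 (6.0/2.5 to 8.5/2.5). These sizes rest on the assumed 5% level and correlations. That the primary result is undefined rests on the text alone.

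**What to change.** Make these changes before anyone sees unblinded data; afterwards the choice cannot credibly be called prespecified.

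1. In section 2.7.1, name one primary scale and one primary time point. One example is LSI-Z, which is listed first, at 12+1 weeks, the end of the intervention. Another single pairing would also resolve the point, and the choice is the sponsor's.
2. In section 3, name the matching group-by-time contrast as the primary analysis and state its alpha.
3. Make the other scale and time point key secondary, tested in a fixed order, each only if the one before succeeds.
4. If both scales must stay primary, state either that both must succeed, each at the full level, or that alpha is split. The first costs power, because both tests must succeed. The second raises the detectable difference from 0.51 to 0.56 SD with 60 per arm.
5. In section 2.7.3, tie the sample size statement to the chosen scale, visit and contrast.

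The cost is a few sentences and a registry update, with no new visits, data or participants. The downside is that the other scale or time point alone can no longer carry the primary claim.

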### 1.2. Study Objective

This randomized controlled trial will (1) examine the effects of a 12-week yoga based intervention focused mainly on physical postures and movements on subjective well-being among healthy but physically inactive elderly Indian aged 60–80 years and(2) study the effect of a yoga based program on multiple secondary health outcomes affecting elderly. The comparison group with equivalent duration will be light exercise focusing on conventional stretching and mobility.

### 1.3. Specific Objectives

The specific objectives of this study are to study the effect of a 12-week yoga-based intervention compared to light exercise focusing on conventional stretching intervention in elderly Indian aged 60–80 years on:Subjective well-being;Prevalent multiple health outcomes such as poor sleep quality, pain, depression anxiety, mood and stress;Balance and fear of falling and physical activity levels;Cognitive function;Cardio-metabolic measures such as blood pressure, blood glucose and blood lipids and on cortisol and other inflammatory markers.

### 1.4. Hypotheses

We hypothesize that compared with light exercise intervention focusing on conventional stretching and mobility; a yoga-based intervention of same duration would result in moderate improvements (20%) in self-reported subjective well-being and similar magnitude improvements on all other secondary outcomes (pain, mobility, sleep, cognition, mood, stress and cardio metabolic and inflammatory markers).

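### The 20% improvement in the hypothesis and the 0.2 in the sample size are different, unlinked quantities, and 120 evaluable participants give about 19% power, not 80%, if 0.2 is a standardised difference

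*Protocol article*

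**What the plan says.** The protocol article gives the anticipated effect in two places.

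- **Section 1.4 (Hypotheses).** Compared with light exercise, yoga "would result in moderate improvements (20%) in self-reported subjective well-being and similar magnitude improvements on all other secondary outcomes". The reference for the 20% is not given. It could be the baseline mean, the comparison-group mean, the scale range or the change from baseline.
- **Section 2.7.3 (Sample Size).** The calculation "is based on the effect size reported in a six month long RCT" of yoga against walking in elderly people, and from it the authors expect "the mean difference (effect size) of around 0.2 on our primary outcome". The figure is called both a mean difference and an effect size, with no unit and no SD. The other stated inputs are "With 80% power, two-tailed significance for the primary between-group comparisons and 1:1 allocation", from which "a total sample of 120 participants is estimated". An assumed 20% dropout brings this to 144 at baseline.

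Sections 1.1 and 2.7.1 name two scales for the primary outcome, LSI-Z and SWLS. Neither the 20% nor the 0.2 is tied to one of them. Section 2.8.1 measures outcomes at 12+1 and 36+1 weeks, and neither figure is tied to a visit.

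**The concern.** A relative improvement and a standardised difference are on different scales and cannot be exchanged without a mean and an SD. The protocol supplies neither, so a reader cannot tell which difference the trial was built to detect.

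This affects the power claim. The one effect named in the calculation, 0.2, does not lead to 120 by the ordinary two-group formula. Depending on which sentence is taken as the target, and on an SD that is not given, the same 120 participants could be ample, about right or far too few. A null result could not then be interpreted properly, because nobody could say what size of effect the trial had a fair chance of finding.

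Section 1.4 also carries the undefined target over to every secondary outcome, from questionnaires to blood markers, although these have quite different units and variability.

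**Working it through.** **Inputs.** From section 2.7.3: effect 0.2, power 80%, two-sided test, 1:1 allocation, 120 evaluable (60 per arm), 20% dropout, 144 at baseline. Not stated, so assumed: alpha 0.05, and 0.2 as a difference in SD units.

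**Step 1. Try to reproduce 120 from 0.2.** For two means, n per arm = 2(1.960 + 0.842)²/d².

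- With d = 0.2: 2 × 7.849 / 0.04 = 392.4, so 393 per arm and 786 in total. The stated total is 120.
- With alpha 0.10 two-sided (equivalently 0.05 one-sided) the total is 620. With alpha 0.20 two-sided it is 452.
- With 0.2 read as Cohen's f (d = 2f = 0.4 for two groups) the total is 198.
- With baseline adjustment the total is multiplied by (1 − ρ²). It is 590, 402 and 150 for ρ = 0.5, 0.7 and 0.9. Reaching 120 needs ρ² = 1 − 120/786 = 0.847, so ρ of about 0.92.

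**Step 2. Repeated-measures routes that do reach 120.** Two were found, each using inputs the protocol does not state.

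- Group × time interaction with f = 0.1, two time points and ρ = 0.7 gives 120. In a 2 × 2 layout this f is a net difference in change of 4 × 0.1 = 0.4 SD. The SD of change is √(2 × 0.3) = 0.775, and 0.4/0.775 = 0.52.
- Between-group effect with f = 0.2, three time points and ρ of about 0.4 gives about 120. Here d = 0.4 on the average of three visits, whose SD is √((1 + 2 × 0.4)/3) = 0.775, and again 0.4/0.775 = 0.52.

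So a repeated-measures calculation could lie behind 120, but in both cases the underlying group difference is 0.4 SD, not 0.2 SD.

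**Step 3. Power and detectable effect with 60 per arm.**

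- Power at d = 0.2: 0.2 × √(60/2) = 1.095, and Φ(1.095 − 1.960) = Φ(−0.865), about 19%. Even with all 144 analysed (72 per arm) it is about 22%.
- Detectable difference at 80% power: 2.802 × √(2/60) = 0.51 by the normal formula, or 0.52 with the t distribution.

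**Step 4. Convert the 20%.** If it is relative to a mean, d = 0.20/(SD/mean). The protocol gives no SD/mean, so a range is shown.

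| SD/mean (assumed) | d | Total N for 80% power | Power with 60 per arm |
|---|---|---|---|
| 0.25 | 0.80 | 50 | 99% |
| 0.30 | 0.67 | 72 | 95% |
| 0.39 | 0.51 | 120 | 80% |
| 0.50 | 0.40 | 198 | 59% |
| 1.00 | 0.20 | 786 | 19% |

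The 20% and the 0.2 coincide only in the last row, where the SD equals the mean. The 20% leads to 120 only if SD/mean is about 0.39.

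**Step 5. Dropout.** 120 × 1.2 = 144 matches the stated figure. This step does not depend on the effect size and does not explain the gap.

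**The case against.** The case against has four parts.

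- **The two figures may not be meant as the same thing.** Section 1.4 states a hypothesis, section 2.7.3 takes 0.2 from an earlier trial, and neither refers to the other. This stands. A reader might infer from the matching digits that the authors treated 20% and 0.2 as one quantity, but the article does not say so.
- **The result does not depend on either figure.** A reader might infer that the trial has no yardstick, or that success could be declared on whichever figure suits. The article does not support this. Section 3 judges the effect by group × time estimates with confidence intervals and effect sizes, neither figure is a success criterion, and section 1.5 calls the trial exploratory. What is missing is a coherent design target, not a way of testing the hypothesis.
- **The word standardised is never used.** This is true, and the 19% is conditional on that reading. It is still the usual sense of effect size. The alternative, 0.2 raw scale points, cannot be turned into a sample size without an SD, which is also absent.
- **A mixed model uses repeated measures, so the plain formula may be too severe.** This stands in part. Correlated measurements can lower the number, but the routes to 120 need either a baseline correlation of about 0.92 or a true difference of 0.4 SD, and the article states neither.

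It is also tempting to convert the 20% with typical values of the well-being scales, or to argue that some secondary scales leave no room for a 20% gain. The article gives no means, SDs or maximum scores that would support this, so neither argument is used.

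**Conclusion.** The point holds as a defect in the design target and the power statement. The article gives two unlinked effect figures, and the one used for the sample size does not deliver the stated power on its natural reading. The gap is 120 evaluable against 786, or about 19% power against 80%. This rests on three assumptions: 0.2 is in SD units, alpha is two-sided 0.05, and the comparison is a plain two-group one.

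It does not follow that the trial is too small for the effect it hopes to see. If the 20% is the real target and SD/mean is 0.39 or less, 120 evaluable would be enough. The article does not allow a reader to decide between these cases.

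**What to change.** - **One target, used twice.** For LSI-Z and for SWLS, state the yoga-minus-exercise difference in scale points, the assumed SD and its source, and the standardised equivalent. Name the follow-up visit to which it applies. Use the same figures in sections 1.4 and 2.7.3. If a percentage is kept, say what it is a percentage of.
- **Restate what 120 delivers.** Give the alpha level. Then either report the detectable effect (about 0.52 SD at 80% power in a plain two-group comparison), or set out the repeated-measures assumptions that justify 0.2: the effect-size definition, the number of time points and the correlation.
- **Secondary outcomes.** Remove the blanket expectation of similar gains and describe these outcomes as estimated with confidence intervals.

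This needs no additional participants and no change to conduct. The cost is one recalculation and a rewrite of sections 1.4 and 2.7.3. The SDs must come from the sponsor's own sources, and where none exists for a scale, an assumed range should be shown.
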